## Abstract

**Introduction:**

Music interventions by listening to recorded music have been associated with the alleviation of breathlessness and the improvement of physical outcomes in the context of pulmonary rehabilitation. Results of these studies, however, should be interpreted carefully since study protocols have been heterogeneous and findings inconsistent. Studies are subject to selection bias and the effect of music interventions is assumed to depend partly on a placebo effect, increasing effectiveness when pre-treatment expectations are higher. In combination with low costs and negligible side effects, implementation of music interventions would be feasible, but they have not been structurally implemented in pulmonary rehabilitation settings yet. Before making efforts on implementing an appropriate music intervention, current use, demands and treatment expectations on music interventions of the target population and their healthcare professionals are to be explored. This study aims to explore the current use of music interventions among patients enrolled in pulmonary rehabilitation and gain insight into the expectations of patients and their caregivers regarding its effect on breathlessness and exercise tolerance.

**Methods and analysis:**

This paper describes the protocol for a cross-sectional survey consisting of a single questionnaire among patients and their healthcare professionals. The questionnaire into expectations regarding music interventions was developed and validated through a systematic and iterative process. After data collection, descriptive statistics will be performed. Cronbach’s alpha will be calculated to measure the questionnaire's internal consistency. Correlation analysis will be performed between baseline characteristics and level of expectation for music interventions.

**Ethics and dissemination:**

This study received approval of the institutional review board of the Erasmus Medical Center, The Netherlands (reference number MEC-2025-0703). Results will be disseminated through a peer-reviewed scientific publication, and raw data will be made available on reasonable request to support implementation.

WHAT IS ALREADY KNOWN ON THIS TOPICMusic interventions have been shown to alleviate breathlessness and enhance exercise tolerance. However, the applicability of previous study findings to real-world populations remains uncertain due to inherent methodological limitations. Consequently, music interventions are not yet routinely integrated into pulmonary rehabilitation practice.WHAT THIS STUDY ADDSThis study will provide insight into the expectations regarding music interventions among patients enrolled in pulmonary rehabilitation programmes as well as their healthcare providers. It will also offer an indication of the feasibility of implementing music interventions in this setting and help identify which patient groups may benefit most based on their expectation profiles.HOW THIS STUDY MIGHT AFFECT RESEARCH, PRACTICE OR POLICYThe results of this study may inform the implementation of music interventions by identifying which patients are most likely to benefit from them. In addition, the study will provide relevant insights into the preferred form and setting of music interventions from the patient perspective, thereby contributing to the design of future randomised studies.

## Introduction

### Music in pulmonary rehabilitation

 Chronic respiratory diseases account for a high disease burden, affecting more than 450 million people worldwide.^1^ Among those, chronic obstructive pulmonary disease (COPD) still contributes to the highest number of disability adjusted life years, even though its incidence is declining.^1
2^ Pulmonary rehabilitation has consistently demonstrated effectiveness in reducing hospital admissions for patients with COPD and other chronic respiratory diseases.^3
4^ It is generally recommended for individuals with either stable or unstable disease to increase fitness or patients experiencing a high symptom burden. Since pulmonary rehabilitation is characterised by its multidisciplinary approach, the scope of treatment possibilities ranges from medical and paramedical to even culturally oriented complementary therapies such as music therapy.^3
5^

Music therapy is an umbrella term encompassing many different forms of music-related interventions, either active/productive or passive/receptive. Specifically in the context of patients suffering from chronic respiratory diseases, active music interventions have shown to be effective. Among patients with COPD, multimodal musical interventions including playing wind instruments or singing have shown to increase pulmonary function outcomes, decrease shortness of breath and increase quality of life.^6–8^ Furthermore, in paediatric patients with asthma, music therapy guided by sessions with certified music therapists has shown to decrease hospital admissions and improve pulmonary function.^9^

### Music therapy versus music interventions

Despite their effectiveness, music therapy sessions, guided singing or playing wind instruments, are likely harder to structurally implement due to the need for certified musical therapists or musicians, additional time investments for patients and higher costs. Also, the interaction between the therapist and the patient can bias the outcomes. The term ‘music intervention’ is typically used to describe treatments involving only listening to recorded music.^10^ The addition of these ‘passive’/receptive music interventions to rehabilitation gained growing attention of researchers in the past few decades as well. Several systematic reviews have investigated the potential benefits of music interventions for patients with chronic respiratory diseases. Although heterogeneity among studies is considerable and findings are inconsistent, evidence suggests that music interventions with listening to recorded music could alleviate breathlessness and improve physical outcomes such as the 6 min walking tests too.^11–14^

Music interventions are generally cheap and very low on side effects, the combination of which would make implementation more feasible than active music therapy.^15^ Nevertheless, structural implementation of music interventions in guidelines in the pulmonary rehabilitation setting is still lacking.

### Challenges in music intervention research

The presence of selection bias is a widely recognised limitation of studies evaluating effects of music interventions. Patients who consent to participate in these studies are assumed to have a natural affinity for music, possibly amplifying the observed effect in the intervention arm and therefore likely limiting generalisation.^16^ Conversely, participants allocated to the control group might nevertheless still listen to music more frequently than the general population if not explicitly prohibited by the study protocol, thereby reducing between-group differences. The extent to which this selection bias influences the study outcomes is unknown and is rarely addressed in papers. Moreover, no studies have specifically quantified the impact of this selection bias as far as is known by the research team. This uncertainty on interpretation poses a significant challenge for further research or implementation.

Another important consideration when interpreting music intervention studies is the underlying mechanism responsible for the observed effect. The effect of music interventions is at least partly attributable to a placebo effect, which is known to increase with higher positive expectations regarding the intervention.^17
18^ However, results of music intervention studies are rarely corrected for treatment expectations as far as is known to the research team. This may be caused by the absence of a validated instrument to measure treatment expectations of music interventions. While several tools have been developed to assess treatment expectations in different fields of medicine, none have been specifically tailored to music-based interventions.^19–21^

Music interventions may only be beneficial for specific patient subgroups. Yet, the patient characteristics that predict favourable outcomes remain undefined. Key determinants could include not only symptom burden or expectations regarding the effect of music interventions but also cultural capital or music listening style. The term cultural capital refers to the non-financial social assets—like knowledge, skills, education and cultural tastes.^22
23^ When considering music listening style, two listening styles are distinguished in current literature: music empathising and music systemising.^24
25^ The distinction is used to address individual differences in musical experiences, preferences and other aspects of musical engagement with a specific emphasis on personality.

Before implementation can be considered, feasibility of music interventions should be assessed. Alhothaly *et al* recently published a study in which relevant factors such as current types of listening activities during exercise and genre preferences among patients in pulmonary rehabilitation programmes in the UK were studied.^26^ Importantly, they found that more than half of participants had no prior experience exercising to music. However, Alhothaly *et al* did not study patient expectations towards music interventions or perspectives of their healthcare professionals, which can be equally relevant. The belief in treatments among healthcare professionals is important to make music interventions effective and integrate them in clinical practice. A preliminary exploration by our research team found substantial variability among healthcare professionals in their views on the potential benefits of music interventions in rehabilitation setting. Addressing these knowledge gaps is essential to develop evidence-based strategies for integrating music interventions into clinical practice.

### Primary objective

The aim of this study is to explore the feasibility of implementation of music listening interventions in the setting of pulmonary rehabilitation by clarifying current use, expectations and demands of such interventions among patients and their healthcare professionals.

### Secondary objectives

To identify associations between baseline characteristics of patients and their expectations of the effect of music interventions on breathlessness or exercise tolerance.To identify differences in expectations regarding music interventions among patients and their healthcare workers.

## Methods and analysis

The study protocol presented here is a cross-sectional survey among patients admitted to pulmonary rehabilitation programmes in the Netherlands and their healthcare workers. Both groups will complete a single comprehensive questionnaire designed to examine the topics of interest integrating previously validated instruments where applicable.

### Setting and participants

In the Netherlands, pulmonary rehabilitation is provided either by general hospitals, university hospitals or by specialised rehabilitation clinics. Outpatient secondary care programmes, typically provided by general hospitals, are most common. These programmes require patients to travel to the hospital or clinics several times a week to participate in exercise sessions under the supervision of specialised exercise therapists or physiotherapists. Additionally, patients attend consultations with other members of the multidisciplinary team such as psychologists or social workers. In the meantime, exercises for home training are usually provided. However, when the patient is in such condition that outpatient rehabilitation is not preferable or possible, tertiary care pulmonary rehabilitation will be offered. Provided only by the dedicated rehabilitation clinics, patients are admitted for multiple weeks (usually 8–12 weeks) to complete the rehabilitation programme. On completion of a programme, patients are referred to dedicated physiotherapists to maintain physical fitness as long as possible.

The study population comprises both patients and healthcare professionals involved in pulmonary rehabilitation. Patient inclusion criteria are as follows: (1) enrolment in a pulmonary rehabilitation programme, either inpatient or outpatient, at secondary or tertiary care level and (2) sufficient understanding of the Dutch language. Exclusion criteria for the study are (1) insufficient understanding of the Dutch language, (2) significant hearing impairment and (3) people who refuse to listen to music due to religious objections.

Healthcare professionals are eligible if they hold a medical or paramedical position at one of the study sites and are actively engaged in pulmonary rehabilitation programmes. Relevant roles include physicians, nurses, physiotherapists, exercise therapists, occupational therapists, speech therapists, psychologists, social workers and dietitians. No exclusion criteria apply for healthcare professionals.

### Study parameters and tools

We used different versions of the same questionnaire in this study: one tailored for patients and another for healthcare personnel. The patient questionnaire comprises five sections addressing the topics of (1) baseline characteristics, (2) cultural capital, (3) dyspnoea severity, (4) music listening habits, exercise and physical activity and (5) expectations from music interventions regarding dyspnoea and exercise tolerance. The version for healthcare professionals will closely mirror the patient questionnaire but will exclude sections on dyspnoea severity, music listening and physical activity. Both versions will be made available in paper format and as an online survey to maximise accessibility.

The first section collects baseline characteristics, including general demographic information such as age, gender and educational level. Depending on the version, additional items address either information on medication use or professional role within the rehabilitation programme. All gathered data will be self-reported, and no information will be extracted from medical records.

The second section covers the topic of cultural capital and music listening type. Cultural capital, a concept widely applied in social sciences, refers to the non-financial social assets—like knowledge, skills, education and cultural tastes.^22
23^ Cultural capital could be important for understanding patients’ expectations of music interventions. We want to figure out whether higher cultural capital leads to higher expectations due to more exposure and possibly more positive experiences accordingly. However, validated tools measuring cultural capital consist of long questionnaires which were considered not feasible to implement in full into our survey increasing the survey burden too much.^27^ Therefore, cultural capital will be assessed using two concise statements to which respondents will state their level of agreement on a 1–7 point Likert scale.

The construct of music listening style is commonly described in the literature through two categories: music empathisers and music systemisers.^24^ The original validated instrument to differentiate between the two comprises 18 questions to which the level of agreement is stated.^24
25^ However, similar to the approach taken for cultural capital, full implementation of this tool was deemed impractical due to concerns about survey length and respondent burden. Therefore, only the two items with the highest factor loadings for each category were selected for inclusion. Consequently, for both the measurement of cultural capital and for music listening type, the outcomes will provide an indicative trend rather than a precise measurement of these constructs.

In the third section, dyspnoea severity was assessed using the Modified Borg Dyspnea Scale, a well-validated tool often used in pulmonary medicine and palliative care to assess dyspnoea severity.^28
29^ The scale consists of two 12-point scale ratings that measure a person’s perceived breathlessness and fatigue. Additionally, four propositions are presented to which patients need to state their level of agreement on a 4-point scale. These statements cover the theme of self-influence on their feeling of breathlessness. Following the questions on dyspnoea, the fourth section covered music listening behaviours and engagement in physical activities. Outcomes will be reported using 5-point scales. Response anchors were developed in collaboration with the experts of experience to make them appropriate for the target population.

The final section of the questionnaire addresses the construct of participants’ expectations regarding the effect of music interventions. As no previously validated instruments on this topic and in this setting were known by the authors, this part of the questionnaire was separately developed specifically for the present study. The subsequent paragraphs describe the process of development of this part of the survey.

The Dutch questionnaires are available in the online supplemental materials. However, in order to increase scientific transparency, we have added an English version of the questionnaire as well in order to enable non-Dutch speaking readers to gain insight into the researched constructs in this study. Translation of the questionnaire was performed using forward and backward translation. The latter of which was performed by an independent researcher that was not previously involved in the development of the questionnaire. It should be noted that the English version of the questionnaire has not been subject to testing or validation in pilot samples, and no psychometric data on this version are obtained. It should be used solely as a tool to increase clarity for all readers of this paper.

### Patient and public involvement

Patient involvement played a central role in the development of this study. Patients, experts by experience in pulmonary rehabilitation, were engaged at multiple stages of the questionnaire validation process. In the initial development stage, a call for voluntary participation was disseminated through the official communication channels of the Lung Foundation Netherlands (Longfonds). All patients who responded were invited to participate in individual online meetings with the researcher.

During these meetings, the questionnaire was evaluated with regard to its content and perceived relevance. Patient experiences were incorporated, and discussions extended beyond question content to include vocabulary, phrasing and response anchors. In this phase, five patients contributed actively to shaping the questionnaire.

In a later phase, additional patients were recruited from the pulmonary medicine ward at the Erasmus Medical Center, Rotterdam, to voluntarily contribute to the further development of the questionnaire. Their involvement in this stage supported the refinement of question clarity and the optimisation of the questionnaire’s formatting. Although no substantial changes to the overall content were made at this point, their feedback was instrumental in enhancing the usability and accessibility of the questionnaire for a broader patient population.

### Data collection and recruitment

Data collection will be conducted over a period of two predetermined weeks at each study site. During this period, members of the research team will visit the different study sites and approach potential participants in person, inviting them for participation. Recruitment will primarily occur after group exercise sessions or during ward visits for patients admitted to rehabilitation clinics. Specific recruitment times will be coordinated in close collaboration with each site. Patients who consent to participate may choose to complete the questionnaire either online or in paper format.

Healthcare personnel will be recruited primarily via email. Email lists will be compiled in cooperation with the participating institutions to identify all staff involved in the pulmonary rehabilitation programmes. Where possible, healthcare workers too will be recruited in person and will be provided with the choice to either fill out the questionnaire online or on paper. In both groups, the online surveys will be available using Microsoft forms, and the data capture programme used is Castor.

### Sample size

The primary objective of this study is to obtain a representative sample of patients currently enrolled in pulmonary rehabilitation programmes. Since no intervention is being tested, a power analysis is not performed. However, it is aimed to reach a target response rate of 40% of all patients admitted to the pulmonary rehabilitation programmes during the weeks of data collection. For healthcare professionals, the target response rate is set at 60%.

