In the introduction of this paper, two methodological challenges in music intervention studies are introduced: the selection bias and the placebo effect. In the future, the questionnaire developed for this study could be valuable in addressing both of these problems. If the questionnaire after this validation study finally will be employed as a baseline measurement for future music intervention studies, it will enable comparisons between included patients and the general population of pulmonary rehabilitation patients, providing insight into the selection bias that might have occurred during the recruitment of patients. Possibly, expectations on music interventions of participants included in new randomised trials are higher than those of the general population, thus confounding outcomes. By incorporating this questionnaire as a baseline assessment, researchers can quantify the extent of selection bias.

Furthermore, because patient expectations will be measured on an ordinal scale in this survey, future analysis could be corrected for patients’ baseline expectations. This might provide valuable information on how treatment expectations influence outcomes, possible discriminating between placebo and an inherent treatment effect. Thus, not only the selection bias, but also the possible placebo effect could be reviewed in a quantitative way when this questionnaire is used in future research. Since selection bias and placebo by expectation are common limitations of many (music intervention-) studies, we advocate measurements of treatment expectations before every music intervention study using the questionnaire developed for this study after completion of its validation process.

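### A 40% response rate is the only stated criterion for a representative patient sample, and no check on non-response is described

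*Protocol article*

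**What the plan says.** The protocol article words the primary objective in two ways. Under Primary objective it reads: "The aim of this study is to explore the feasibility of implementation of music listening interventions in the setting of pulmonary rehabilitation", to be done by describing what patients and staff now use, expect and want. Under Sample size it reads: "The primary objective of this study is to obtain a representative sample of patients currently enrolled in pulmonary rehabilitation programmes".

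The Sample size section omits a power analysis because no intervention is tested. Its one patient criterion, applied while the survey runs at the sites, is this: "it is aimed to reach a target response rate of 40% of all patients admitted to the pulmonary rehabilitation programmes". The staff criterion has the same form: "For healthcare professionals, the target response rate is set at 60" per cent. Neither a number of questionnaires nor a precision is given.

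Recruitment is in person over two weeks per site (Data collection and recruitment): "Recruitment will primarily occur after group exercise sessions or during ward visits for patients admitted to rehabilitation clinics". All data are self-reported, with nothing taken from medical records (Study parameters and tools), and returned answers cannot be traced (Ethics and dissemination).

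The section on potential limitations, strengths and future use admits a risk of selection bias. Its answer is to present the study as one on non-pharmacological interventions, with the research team giving that framing in person and in a standard way. The same section says that, if the questionnaire is later adopted as a baseline measure in music trials, "it will enable comparisons between included patients and the general population of pulmonary rehabilitation patients".

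**The concern.** A response rate counts how many people answered. It does not say whether they resemble those who did not. A sample can reach 40% and be badly skewed, or miss 40% and be sound.

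This matters more here than in most surveys. The Introduction criticises earlier music studies because people who consent probably have an affinity for music, and notes that the effect of this has not been quantified. If the survey sample leans the same way, a later trial compared against it would appear less selected than it is.

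Timing matters too. Responders cannot be matched to site lists afterwards, so whatever is to be known about decliners has to be noted in aggregate while recruiters are on site.

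**Working it through.** **Inputs.** From Sample size: response rate r = 0.40 for patients and 0.60 for professionals. The documents do not give the number of questionnaires n, the difference d between responders and non-responders, or the inpatient share. Values used for these below are assumptions. The 40% is a declared target with no formula behind it, so there is no figure to reproduce.

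**1. Non-response bias.** The population proportion is p = r·pR + (1 − r)·pN, with pR for responders and pN for non-responders. Hence bias = pR − p = (1 − r)·(pR − pN) = (1 − r)·d.

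- Patients: 0.6 × 5 = 3 points; 0.6 × 10 = 6; 0.6 × 20 = 12; 0.6 × 30 = 18.
- Professionals: 0.4 × 10 = 4 points; 0.4 × 20 = 8.

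The number of questionnaires does not enter the formula.

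**2. Against sampling error.** The 95% half-width at p = 0.5 is 1.96·√(0.25/n). The finite-population version takes N = n/0.40.

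| Assumed n | Half-width | With finite-population correction |
|---|---|---|
| 100 | ±9.8 points | ±7.6 points |
| 200 | ±6.9 points | ±5.4 points |
| 400 | ±4.9 points | ±3.8 points |

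A 6-point bias is within sampling error at n = 100 and outside it at n = 400. Coverage of the nominal 95% interval (no correction) is Φ(1.96 − b/se) − Φ(−1.96 − b/se), with se = √(0.25/n). For b = 0.06 it is 78% at n = 100, 60% at n = 200 and 45% at n = 300. More questionnaires make the interval narrower but do not move its centre.

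**3. Setting mix.** Pooling bias = (inpatient share in sample − inpatient share in population) × (difference between settings), with overall response held at 40%.

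- Low case: population share 20%, inpatient response 60%. Outpatient response = (0.40 − 0.20 × 0.60)/0.80 = 0.35. Sample share = 0.20 × 0.60/0.40 = 30%. With a 10-point difference, bias = 0.10 × 10 = 1 point.
- High case: population share 30%, inpatient response 80%. Sample share = 0.30 × 0.80/0.40 = 60%. With a 20-point difference, bias = 0.30 × 20 = 6 points.

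The bias is zero if response rates are equal across settings, or if expectations are.

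**4. What the stated mitigation covers.** Standardised neutral framing acts on one route into non-response, refusal because the topic is music. It does not act on patients who are never approached, who decline any survey, or who take a form and do not return it. It also produces no data from which the remaining bias could be judged.

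**The case against.** The article is a condensed account, and recruitment logs commonly sit in a full protocol that is not shown. A rate calculated over all patients in the programmes needs a count of those patients, so some aggregate information must be planned. Anonymous answers do not prevent anonymous tallies. The article admits the selection risk and takes a step against its most plausible cause. The reference use is conditional, concerns the questionnaire's future, and is not among the objectives. Weighting is often left to an analysis plan. The differences assumed above are not from the documents, and the 40% denominator may include ineligible patients, so not all of the remaining 60% is non-response among eligible patients.

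Much of this stands, and it rules out three stronger readings that a reader might infer.

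- *Nothing is recorded about non-responders.* The text is silent on this; it does not say so. Nor does anonymity make comparison impossible, because aggregate counts remain open.
- *Inpatients are easier to reach and will be over-represented.* The article says "Outpatient secondary care programmes, typically provided by general hospitals, are most common", but it also has outpatients attending several times a week, with recruitment after group sessions. It gives no reach or response by setting and no explicit plan to report only a pooled figure.
- *The estimate cannot serve as a reference.* Bias is possible and unquantified; it has not been shown.

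The objection does not reach the stated design decision. The text names representativeness as the objective, sets a response rate as its sole patient criterion, and words the primary objective differently elsewhere.

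**Conclusion.** The point holds in a limited form. The plan's criterion for representativeness does not measure it, and no means of checking or adjusting for non-response is described. At the target rate the bias is 0.6 times the responder/non-responder difference, or 6 to 18 points if that difference is 10 to 30 points. The multiplier follows from the plan; the differences are assumptions. Setting mix is a secondary route, worth about 1 to 6 points under the assumptions shown and possibly nothing.

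The survey remains useful for its feasibility aim. The claim to be representative, and the conditional use as a population reference, need support that the article does not yet give. The two wordings of the primary objective need reconciling in any case.

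**What to change.** 1. During the two-week window, have recruiters keep an anonymous aggregate tally of patients approached, accepting and declining, by setting, site, sex and age band. Ask each site for its enrolled count by setting, which the 40% denominator largely needs anyway. State whether that denominator means everyone enrolled or only new admissions.
2. Record setting on the questionnaire if it is not already there. Report main results separately for inpatient and outpatient programmes, and give an overall figure weighted to the enrolled counts. Compare responders with non-responders using the tally.
3. Bring the objective in Sample size into line with the Primary objective section. Call the sample representative only as far as these checks support it.

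Worst-case bounds beside each proportion are optional. At 40% response they are always 60 points wide: an observed 60% gives 0.40 × 0.60 = 24% up to 24% + 60% = 84%.

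The cost is minor work for recruiters who are already on site, a request for site totals, and slightly wider weighted intervals. None of it requires identifiable data.
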